### Research questions

The following research questions are proposed in this study:What are the effects of the HS project interventions on the physical fitness and motor development of preschool children, as well as on their cognitive and social competencies?How do intervention effects differ among the HS group, the OPE group, and the FP group?To what extent are the intervention gains on the HS groups mediated by personal factors?What are the main social-ecological variables related to differences in the intervention outcomes?To what extent are the outcome variables related to each other?

### Hypotheses

Based on these five research questions, we hypothesize that children in all groups will exhibit improvements in developmental outcomes across the 10-week period. We predict participants in the HS groups will report significantly higher scores on physical fitness, FMS, and cognitive self-regulation tests at follow-up, compared to baseline. We also expect improvements in these indicators to be significantly greater when compared to the alternative programs (OPE and FP).We also hypothesize that differential intervention effects within the HS groups will be associated with the individual, family, and environmental factors.

### Methods and design

#### Study design

A quasi-experimental design study will be employed.

At the beginning of the September 2021 school semester, preparations and baseline data collection will be carried out over 2 weeks, with an intervention period running for 10 weeks. This will be followed by a posttest period and a 6-week follow-up. At the beginning of the February 2022 semester, the third round of testing will be conducted. Given the uncertainty of the pandemic, if the school temporarily closes again, the project will be postponed until the next semester or the next opportune time.

This study’s procedures are illustrated in Figure 2.

**Figure 2. f2:**
[figure not shown]
Study procedure. HS: Hello Sunshine PE curriculum; OPE: Ordinary PE curriculum; FP: Free play PE

## Participants

The study will be conducted in three types of kindergartens in the center of Haikou city, China. Sport-featured kindergartens, public kindergartens, and inclusive private kindergartens in the same district will be assigned. Two classes in K2–K3 grade (children aged 4–6 years) will be randomly selected from these kindergartens and will be allocated as HS group (from sport-featured kindergarten), OPE group (from public kindergarten), and FP group (from inclusive private kindergarten).

The inclusion criteria are: 1) healthy and typically developing children willing to participate, 2) aged 4–6 years, 3) with the informed consent of their primary caregivers, 4) the primary caregiver must have a smartphone to answer the questionnaire. Children 1) who have difficulty in communication, unexplained health problem, 2) who have a contraindication to exercise such as congenital heart disease, asthma, fever, malaise, diarrhea, and 3) who have additional training from a sports club will be excluded.

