**Findings::**

If this intervention provides evidence that these skills improve children’s multidimensional development, it will support the promotion of similar programs in China. We will also outline the social-ecological factors affecting the intervention’s results, providing further information for improving pedagogical methods related to preschool ball skills.

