## Materials and methods

The study protocol complies with the guidelines of the SPIRIT 2013 statement (Chan *et al.*, 2013). The trial was registered with the Chinese Clinical Trial Registry (registration number: ChiCTR2000035414) on 10 August 2020 and will be carried out in accordance with the Declaration of Helsinki.

Children, aged 4–6 years, from three predetermined kindergartens will participate. The three kindergartens are categorized based on three different PE programs provided for the children: a Hello Sunshine (HS), an ordinary PE (OPE), and a free play (FP) depending on their existing PE curriculum.

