## Randomization

The children aged 4–6 years within four classes (two classes selected from K2 and K3 grade, separately) will be randomized from the designated kindergartens using Research Randomizer software. The preschoolers in each class who meet the eligibility criteria will be screened by the kindergarten teachers and staff. To avoid changes in teachers and classmates affecting the results of this course, we will intervene in the form of a nature class. In total, 12 nature classes in grades K2 and K3 from the 3 kindergartens will be assigned to a PE curriculum in their respective schools, that is, 4 classes in the sport-featured kindergarten with “Hello sunshine” PE curriculum, the OPE group will have ordinary PE classes, the PE class in the FP group will be free play. This sequence will then be concealed in an opaque envelope.

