### Covariate and mediator

#### Personal factors

Age will be calculated as the children’s month-based ages, as it is going to affect the intervention’s outcome. Participants’ perceived motor competence will be measured with a pictorial scale for perceived movement skill competence (PMSC) that builds upon the TGMD-2 (Barnett *et al.*, 2015). It consists of 13 pictures illustrating cartoon boys (boy version) or girls (girl version) performing TGMD-3 skills. It shows middle to high instrument reliability and face validity in Chinese children (Diao *et al.*, 2018). Children will be shown illustrations by the examiner and judge whether the cartoon character is good at doing the skills, then choose between four Likert scale options (1 to 4, from “not too good” to “really good”).

Individual temperaments are expected to be predictive of the differential effects of this motor skills intervention (Taunton *et al.*, 2018), and they will be assessed using the 36-item Children’s Behavioral Questionnaire-Very Short Form (CBQ-VSF) (Putnam and Rothbart 2006). The test is divided into three broad dimensions: surgency, negative affect, and effortful control and it demonstrates acceptable internal consistency. It is a very short form based on the well-established parent report measure of temperament CBQ questionnaire for children aged 3 to 8 years (Rothbart *et al.*, 2001) and it has medium to high reliability and validity confirmed by studies in multiple countries. The CBQ-VSF provides moderate reliability of scale scores for assessing temperamental characteristics in preschoolers (de la Osa *et al.*, 2014).

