## Results

Data will be imported from Excel 2019 to IBM SPSS version 26.0 for inferential statistical analysis. The normal distribution of the data will be checked before determining the descriptive statistics for all variables (means and standard deviations). The participants’ basic information will be descriptive, including age, gender, and BMI. The primary outcomes will be expressed as continuous. If data are approximately normal distribution, the effect of the PE curriculum intervention on dependent variable (FMS, or TGMD, or HTKS, or SCEB score) will be investigated with repeated ANOVAs within factor: time (pre and post), between factors: group (HS, OPE, and FP) and gender (boy and female) and Bonferroni post hoc tests. Further, the relationship between FMS and other domains will be identified by regression analysis. Finally, the potential influence of individual factors (such as age, gender, and temperament) on the intervention effect will be investigated by comparing the gain in FMS score and subscale. Multiple regression equation is used to further explore the extent to which social-ecological factors contribute to the FMS score level at baseline. Statistical significance will be set at *P* < 0.05.

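### Each arm is a single kindergarten of a different type, so curriculum and kindergarten cannot be separated. The Randomization section obscures this, and the effect model omits age and family background.

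*Protocol article*

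**What the plan says.** Materials and methods fixes the sites in advance: "Children, aged 4–6 years, from three predetermined kindergartens will participate". It sorts them into the three programmes "depending on their existing PE curriculum". Participants then ties each arm to one type of kindergarten: classes "will be allocated as HS group (from sport-featured kindergarten), OPE group (from public kindergarten), and FP group (from inclusive private kindergarten". Study design gives the label: "A quasi-experimental design study will be employed".

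The Randomization section says that classes are drawn at random within the designated kindergartens and that the 12 classes follow the curriculum of their own school. It closes with: "This sequence will then be concealed in an opaque envelope".

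Under Personal factors, age is to be recorded as "month-based ages, as it is going to affect" the outcome. That section and the Family factors and Environment factors sections also collect temperament, parental education and occupation, after-school activity and home play space, all under the heading Covariate and mediator. Results specifies the effect analysis as a repeated-measures ANOVA with time (pre, post) within children and "between factors: group (HS, OPE, and FP) and gender (boy and female"), followed by Bonferroni post hoc tests. Individual factors are used there to compare FMS gains, and social-ecological factors in a regression on baseline FMS.

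The Abstract says that, if the intervention yields evidence of benefit, "it will support the promotion of similar programs in China". Strengths and limitations calls for randomised trials in more kindergartens. It does not mention confounding by kindergarten type or family background.

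**The concern.** There are three separate faults.

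- **Aliasing.** With one kindergarten per arm, a difference in gain between HS and OPE may come from the curriculum, the staff, the facilities, the children enrolled or anything else that differs between a sport-featured and a public kindergarten. The data hold no information to apportion it.
- **Contradictory wording.** The Randomization heading and the envelope sentence suggest a protection against selection that does not exist. The arm is settled by the kindergarten before any class is drawn, so there is no allocation sequence to conceal.
- **Model at odds with the article's own account.** A variable said to affect the outcome is left out of the model that estimates the effect, as are the family covariates collected.

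Baseline is also uncertain. Materials and methods and Strengths and limitations both say that the kindergartens keep their existing curricula, so HS children may have had HS before the first measurement. The documents do not show which way that would bias the result.

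What is at stake is the hypothesis that HS children improve more than OPE and FP children, and the policy use that the Abstract and Conclusions foresee.

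**Working it through.** **1. Degrees of freedom.** There are three kindergartens and three arms, so 3 - 3 = 0 degrees of freedom remain for variation between kindergartens within an arm. The four classes per arm do not help, because all four sit in the same kindergarten.

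**2. What is random.** Set side by side, Materials and methods (predetermined kindergartens, arm by existing curriculum), Participants (arm by kindergarten type) and Randomization (classes drawn within a kindergarten, curriculum of their own school) agree on one reading: random selection of classes and no random allocation. Only the section heading and the envelope sentence do not fit it.

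**3. What the model removes.** With two time points, the group-by-time test compares mean gains. A stable difference in level between kindergartens cancels. A difference in 10-week growth by age, background or kindergarten does not. For the same reason, a fixed covariate entered only as a main effect leaves the group-by-time contrast unadjusted. It must also interact with time.

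**4. Size, as an illustration.** The documents give no between-kindergarten variance, so its share of the variance in gains, τ², is assumed to be 0.02 to 0.05, with gains scaled to SD 1. From the documents come 83 children per arm, two-sided 5% (sidedness assumed) and Bonferroni, read as three pairs: 0.05/3 = 0.0167 per pair.

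- SE used by the test if kindergarten is ignored: √(2/83) = 0.155.
- Critical difference: with Bonferroni 2.394 × 0.155 = 0.372; without it 1.96 × 0.155 = 0.304.
- True SD of the contrast under no curriculum effect: √(2(1 - τ²)/83 + 2τ²).
- Rejection probability: 2 × [1 - Φ(critical difference / true SD)].

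| τ² (assumed) | SD from kindergarten alone, √(2τ²) | True SD of contrast | Rejects, Bonferroni | Rejects, uncorrected |
|---|---|---|---|---|
| 0.02 | 0.20 | √(0.0236 + 0.04) = 0.252 | 14% | 23% |
| 0.05 | 0.32 | √(0.0229 + 0.10) = 0.351 | 29% | 39% |

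If the test's SE is taken from the within-kindergarten variance instead, √(2(1 - τ²)/83), the results are 14.5% and 30.1% with Bonferroni, and 23.2% and 39.8% without. The term 2τ² does not contain the number of children, so a larger sample does not shrink it.

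**The case against.** The case for the plan is substantial, and several parts of it stand.

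- **Openness about the design.** The article calls itself quasi-experimental more than once and states plainly that arm follows kindergarten. A reader might infer from the Randomization section that the trial is presented as randomised. The document as a whole does not support that. The fault is a heading and one sentence that contradict the rest.
- **Pre-post comparison.** A reader might infer that every difference in age or background passes into the HS contrast. It does not, because stable level differences cancel and only differential growth remains.
- **Restrictions in the design.** The kindergartens are in one district, K2 and K3 classes are drawn in each, and children with extra sports-club training are excluded. Because grade is balanced by design, its absence from the model is a weak complaint. Age in months within grade is a different matter.
- **Bonferroni.** The uncorrected 23-39% does not describe the planned post hoc test. The figure that does is 14-29%.
- **Family choice.** It is tempting to say that sporty families choose the sport-featured kindergarten. Nothing in the article describes how children enrol, so this is conjecture and the point does not need it.
- **Conditional claims.** The Abstract's policy sentence depends on evidence of benefit being found, and the limitations ask for randomised trials in more kindergartens.
- **A condensed article.** A fuller plan may use the covariates further. But Results does state the effect model, so this answers the point only in part.

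None of this restores the missing degrees of freedom, gives the concealed sequence a meaning, or puts age into the effect model.

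**Conclusion.** The point holds, and it needs correction before the results are interpreted. Group is fully aliased with kindergarten. The concealment statement contradicts the design described elsewhere. The stated effect model omits a variable that the article itself says matters. The limitations do not name confounding by kindergarten type or family background.

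Under the assumed 2-5% share, the corrected pairwise test of a true null rejects about 14-29% of the time, roughly 8 to 17 times its nominal 1.67%. These rates rest entirely on that assumption and show how a small kindergarten effect is magnified. They do not estimate the bias in this trial. The aliasing itself needs no assumption.

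**What to change.** 1. **Effect model.** Adjust the group-by-time contrast for age in months and a short prespecified set of covariates already collected: sex, parental education and after-school activity. Give each its interaction with time. Enter education and activity as scores or collapsed categories. Beyond gender, which is already in the model, age plus two scores costs about three degrees of freedom for the contrast (education of one parent). Entering every factor as recorded costs far more: occupation alone has seven categories (6 df) and activity five (4 df). This reduces measured confounding only. It does not separate curriculum from kindergarten.
2. **Randomization section.** Rename it as random selection of classes and delete the sentence on the concealed sequence. This costs nothing.
3. **Claims.** State in the Abstract, Strengths and limitations, and Conclusions that the results compare three kindergartens, that curriculum and kindergarten effects cannot be separated, and that children may have been exposed to the existing curriculum before baseline. The cost is a weaker claim. Only several kindergartens per arm would support a stronger one, and the article already leaves studies in more kindergartens to future work.

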## Sample size determination

We used WinPepi software to calculate the sample size with reference to Westendop’s research (2014) while ensuring it would be larger than those used in other comparative studies (Robinson *et al.*, 2017; Taunton, Mulvey and Brian, 2018). The following assumptions were used: significance level of 5%; power of 80%; and confidence level of 95%, inflated to compensate for a 5% non-inclusion rate. As a result, at least 249 children (83 in the HS group, 83 in the OPE group, and 83 in the FP group) will participate in this study.

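### The 80% power claimed for 83 children per arm is not supported by its listed assumptions, which allow for neither the intact classes nor the Bonferroni-corrected comparisons

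*Protocol article*

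**What the plan says.** The Sample size determination section opens with "We used WinPepi software to calculate the sample size with reference to" an earlier study, and adds that the number was kept above those of comparable studies. It then lists its assumptions: "significance level of 5%; power of 80%; and confidence level of 95%, inflated to compensate for a 5% non-inclusion rate". From these it concludes that "at least 249 children (83 in the HS group, 83 in the OPE group, and 83 in the FP group) will participate".

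Two other sections fix features that bear on this number.

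- **Randomization:** to keep teachers and classmates constant, "we will intervene in the form of a nature class". There are 12 such classes, four in each of three kindergartens, and each kindergarten supplies one arm.
- **Results:** the analysis is a repeated-measures ANOVA with time (pre, post), group (HS, OPE, FP) and gender as factors, followed by "Bonferroni post hoc tests" at an overall 5% level.

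The Hypotheses section predicts greater improvement with HS than with either OPE or FP, so pairwise comparisons carry the main claim.

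**The concern.** The power figure is presented as the product of a listed set of assumptions, and that list does not describe the trial that the rest of the article sets out. Children in one class share a teacher, lessons and playmates, so 79 children in four classes carry less information than 79 independent children. A Bonferroni correction over three pairs tests each pair at 0.0167 rather than 0.05. Either feature lowers power for a given difference, and the list allows for neither.

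The consequence lies in how a null result is read. The article has a policy aim. If HS does not differ significantly from OPE or FP, a reader who relies on the 80% will take that as fair evidence of no useful benefit. If actual power is well below 80%, that reading is unsafe.

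**Working it through.** **Inputs from the article.** Significance 5% (taken as two-sided), power 80%, 5% non-inclusion, 83 per arm, three arms, 12 classes, Bonferroni tests.

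**Inputs assumed.** ICC 0.02 to 0.10, and a comparison of two group means at a single time point with SD 1. The article gives no effect size, SD or ICC.

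**Step 1: the plan's own figure.** Without an effect size, 83 cannot be reproduced directly, so I work back.

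- Evaluable per arm: 83 × 0.95 = 78.85, about 79. (83 / 1.05 = 79.05 gives the same.)
- Two-sample t-test, n = 79 per arm, 156 df, alpha 0.05, power 80%: d = 0.449.
- By the normal approximation, d = 0.45 needs 78 per arm, and 78 / 0.95 rounds up to 83.

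So 83 matches one unadjusted comparison of individual children at about 0.45 SD. This is an inference, not something the article states. The noncentrality is 0.449 × √(79/2) = 2.82.

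**Step 2: Bonferroni only.** Same noncentrality, 156 df.

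- Three pairs, alpha 0.05/3 = 0.0167: power about 66%.
- Two pairs (HS against each of the others), alpha 0.025: power about 71%.

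This loss hardly depends on d. If n is sized for 80% in one unadjusted test, power at 0.0167 is 65.7% for d = 0.3, 65.5% for d = 0.45 and 64.8% for d = 0.8.

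**Step 3: class clustering.** Class size m = 79/4 = 19.75. Design effect DE = 1 + (m − 1) × ICC = 1 + 18.75 × ICC. Noncentrality = 2.82 / √DE. Degrees of freedom = 12 classes − 3 arms = 9.

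| ICC | DE | Noncentrality | Power, alpha 0.05 | Power, alpha 0.0167 |
|---|---|---|---|---|
| 0.02 | 1.38 | 2.40 | 57% | 36% |
| 0.05 | 1.94 | 2.03 | 44% | 25% |
| 0.10 | 2.88 | 1.66 | 32% | 16% |

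At ICC 0.05 the difference detectable with 80% power is about 0.70 SD, or 0.86 SD at the Bonferroni level, against 0.45 SD in Step 1.

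**Step 4: sensitivity to the pre-post design.** The planned group effect is a difference in change. With pre-post correlation r and equal variances, the SD of change is √(2(1 − r)) times the raw SD.

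- At r = 0.5 the factor is 1, so Steps 2 and 3 stand. Below 0.5 power is lower still.
- At r = 0.7 the factor is √0.6 = 0.775, and 0.449 / 0.775 = 0.58 on the change scale. Bonferroni-only power is about 89%. With clustering at alpha 0.05 and 9 df it is about 79% at ICC 0.02 and 64% at ICC 0.05.

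**Step 5: sensitivity to the target effect.** If the unstated target were d = 0.8, power with 79 per arm and 9 df would be 97% at ICC 0.02 and 89% at ICC 0.05 without Bonferroni, and 88% and 74% with it.

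**The case against.** A reader might infer that the design has been shown to lack 80% power. The article does not support that. Power is defined against an effect size, and none is given. The target may sit in the cited study or in a fuller protocol, and the number was also kept above those of comparable studies, so some margin is possible. Step 5 shows that a target of 0.8 SD would mostly still be powered. That objection stands against a flat statement of underpowering. It does not rescue the claim as printed: at 0.8 SD the listed inputs call for about 26 per arm, not 83, so a large target does not explain the number either.

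The pre-post analysis is the second good objection. At r = 0.7, Bonferroni alone no longer pulls power below 80%. This stands too, and it makes the single-time-point figures illustrative. At ICC 0.05 a shortfall remains even then.

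Third, the analysis as described names no class term, so the 9-df figures belong to a comparison that respects the classes. That is fair, but a child-level analysis would keep its nominal power only by accepting too many false positives, so the 80% would mislead in that case as well.

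Two lesser matters are not findings on their own. A condensed article may leave the effect size to a fuller document, and the 95% confidence level merely restates the 5% significance level.

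**Conclusion.** The concern holds in a limited form: the 80% is unsupported by the assumptions listed for it, because they omit two features that the same article fixes. It is not shown to be false.

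The size of the gap is conditional. It assumes that 83 was sized for 80% power in one unadjusted comparison of individual children (implied d about 0.45, back-solved), a single-time-point model, and ICCs that are mine. On those terms power is about 66% with Bonferroni over three pairs, 57% to 32% with clustering over ICC 0.02 to 0.10, and about 25% with both at ICC 0.05. A strong pre-post correlation or a larger target effect would reduce or remove the gap.

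None of these figures covers differences between kindergartens. Each arm is one kindergarten, so kindergarten and programme are fully confounded, and a class-level design effect does not address that. Adding children would not address it either.

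**What to change.** Keep 249 children and rewrite the power statement in the Sample size determination section:

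1. State the outcome and effect size (with SD) assumed.
2. Report power and detectable difference for the planned pre-post group comparison, at the Bonferroni alpha actually used, with the number of pairs stated.
3. Apply the design effect 1 + (m − 1) × ICC with class-level degrees of freedom, over a range of ICCs (for example 0.02 to 0.10) and of pre-post correlations.
4. Say that these figures exclude kindergarten-level variance, because each arm is a single kindergarten.
5. While editing, drop the 95% confidence level from the list of inputs.

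The cost is a few sentences and a small table, with no extra children and no change to delivery. The downside is that the stated power will look less favourable.
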